### Study Design

The study uses a mixed methods, nonrandomized, multiple-baseline, within-subject design consistent with SCED methodology. The multiple baselines will be operationalized via 3 repeated preintervention assessments (at −2 weeks, −1 week, and week 0) to establish outcome measure stability. Afterward, participants will commence the 6-week intervention simultaneously. Participant or researcher blinding is not possible. Data collection points are shown in Table 2.

**Table 2. T2:** Data collection points.

	Screening (–4 wk)	Baseline 1 (–2 wk)	Baseline 2 (–1 wk)	Baseline 3 (0 wk)	Midintervention time point (3 wk)	Postintervention time point (6 wk)
Demographics (ie, age, gender, ethnicity, educational level, employment status, and treatment status [ie, in treatment or in remission or cancer free])	✓	✓				
Psychological well-being (SWEMWBS^a^) [55]		✓	✓	✓	✓	✓
Psychological distress (K10^b^) [56]		✓	✓	✓	✓	✓
World Health Organization quality of life instrument social domain subscale [57]		✓	✓	✓	✓	✓
Two global items (health and QoL^c^) from the EORTC QLQ-30^d^ [58]		✓	✓	✓	✓	✓
Exit survey (for dropout participants; Multimedia Appendix 3)—to be administered at any exit point						

a

SWEMWBS: Short Warwick-Edinburgh Mental Wellbeing Scale.

b

K10: Kessler Psychological Distress Scale.

c QoL: World Health Organization Quality of Life social domain subscale.

d

EORTC QLQ-C30: European Organisation for Research and Treatment of Cancer Quality of Life Questionnaire Core 30.

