**Exclusion criteria**
Current or previous participation in shared reading specificallyWomen and gender-diverse people with cancer of unknown primary or gynecological cancer as secondary (ie, affected by multiple cancers, but primary cancer is unknown)Current receipt of other psychological interventions (ie, counseling or cognitive behavioral therapy)Inability to comprehend the study and/or provide informed consent (ie, insufficient command of the English language in the absence of someone who can adequately interpret)

As this is not a full-scale trial, nor is the primary aim to evaluate the effectiveness of online SR, a formal sample size calculation was not required [52,53]. Instead, the target sample was determined based on 2 factors. First, single-case experimental design (SCED) methodology requires a minimum of 3 participants to demonstrate an experimental effect [54]. Second, the traditional SR model typically consists of 2 to 12 attendees [32]. Consequently, this feasibility study will aim to recruit between 4 and 10 participants and will not be designed or powered to evaluate the effectiveness of online SR; the absence of a comparator condition and the small sample size will preclude inferential conclusions about efficacy.

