### Recruitment

International study recruitment is planned from November 2025 to March 2026. Potential participants will be identified through clinician referral at patient identification centers within the South Central Regional Research Delivery Network and via study posters displayed in oncology waiting rooms. If required to meet recruitment targets, the study will also be promoted internationally, via cancer charities and social media platforms (ie, LinkedIn, X [formerly known as Twitter], and Facebook). Interested parties will contact the lead author ([name]) directly and will be asked to complete a consent form and a screening and demographics questionnaire, as well as 3 weekly staggered baseline outcome measures (Multimedia Appendix 2). These data points will be collected via Qualtrics (Qualtrics International Inc), the same online platform where participants will indicate their availability for taking part in the online SR intervention.

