### Strengths and Limitations

The study’s use of a multiple-baseline SCED enables in-depth individual-level analysis despite the small sample size. Additionally, the study uses a mixed methods approach alongside an RE framework [51] to explore not only whether online SR is a feasible and acceptable intervention but also for whom and under what conditions. Finally, the intervention development was informed by PPIE from design to dissemination, ensuring that the online SR model was shaped alongside the people it aims to support.

However, consideration must be given to issues of equity and inclusivity in the design and delivery of the online SR intervention, including potential limitations in accessibility for individuals with lower digital literacy, limited educational opportunities, or neurodivergence and specific learning difficulties. Such factors may risk inadvertently excluding those who could benefit most from community-based psychosocial interventions. However, SR is intentionally designed to be open and participatory, accommodating a wide range of abilities and preferences; sessions emphasize listening as much as reading, and there is no expectation for participants to interpret texts in a particular way or even verbally contribute. This flexibility will allow individuals to engage with online SR at their own comfort level, supporting inclusion while preserving online SR’s ethos of shared, reflective connection through literature. Future refinement could explore the barriers to engagement among people who decline or withdraw from the online SR intervention to better understand their motivations and inform strategies to improve uptake and retention.

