### Conclusions

This feasibility study will be the first to examine online SR as an adjunctive psychosocial intervention for people affected by gynecological cancers. In doing so, the proposed intervention responds to a recognized gap in accessible, low-intensity psychosocial support for this population. Importantly, it may offer community-based peer support for those managing emotional distress who may prefer not to engage with or lack access to formal therapeutic support.

While the study is exploratory, it will offer foundational data on the acceptability, feasibility, and preliminary efficacy of online SR. Additionally, it will inform the potential intervention development components of a future, adequately powered, full-scale trial. Should the study demonstrate online SR to be feasible and acceptable, implications include having a scalable, low-cost model that could be embedded alongside existing survivorship pathways. Finally, its fully online delivery has potential to reach those facing geographical, financial, or psychological barriers to formal care, supporting more equitable access across diverse health system settings.

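### The study is labelled a multiple-baseline single-case design, but everyone shares one baseline schedule and one start, so intervention phase cannot be separated from shared time

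*Protocol article*

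**What the plan says.** The Study Design section describes a "nonrandomized, multiple-baseline, within-subject design consistent with SCED methodology". It then defines the term: "The multiple baselines will be operationalized via 3 repeated preintervention assessments", at −2, −1 and 0 weeks, to check that the measures are stable. The next step is a common start: "Afterward, participants will commence the 6-week intervention simultaneously". Table 2 gives one assessment schedule for all participants. Intervention Development and Content describes one set of six weekly group sessions at a fixed day and time.

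The Recruitment section says that participants complete "3 weekly staggered baseline outcome measures".

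The sample-size paragraph after Textbox 1 gives two reasons for recruiting 4 to 10 people. The first is that SCED "methodology requires a minimum of 3 participants to demonstrate an experimental effect". The second is that shared reading groups usually have 2 to 12 attendees. The paragraph also states that "the absence of a comparator condition and the small sample size will preclude inferential conclusions about efficacy".

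The multiple-baseline label appears in the Abstract (Methods) as well. Strengths and Limitations presents it as a strength: the study's "use of a multiple-baseline SCED enables in-depth individual-level analysis despite the small sample size". The Conclusions say that "it will offer foundational data on the acceptability, feasibility, and preliminary efficacy of online SR".

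**The concern.** In a multiple-baseline design, the intervention starts at different times in different participants. If each person's scores shift after their own start, while those still in baseline stay level, a shared calendar influence is an unlikely explanation. Several pretests before one common start do not provide that comparison. They make a before-after series repeated across people.

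Three things depend on the label. The reader is told that the study has a form of experimental control that it lacks. One of the two sample-size reasons relies on showing an experimental effect. The secondary outcomes (well-being, distress and quality of life) may be read as evidence about the intervention when they can only show change during the weeks in which it ran.

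**Working it through.** There is no power calculation to reproduce. The two stated reasons (at least 3 participants; 2 to 12 attendees) overlap at 3 to 12. The target of 4 to 10 lies inside that range but is not derived from it. The check is therefore structural.

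**Inputs.** Assessment weeks −2, −1, 0, 3 and 6 (Table 2); a common start after the week 0 assessment (Study Design); n from 4 to 10 (sample-size paragraph).

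**1. Is any staggering described elsewhere?** The word *staggered* in Recruitment refers to weekly questionnaires within a person. The recruitment window (November 2025 to March 2026) does not create different starts, because the intervention begins in May 2026 and Table 2 counts the baselines from that start. No section gives tiers, different baseline lengths or different start weeks. Distinct start points: 1.

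**2. Can intervention phase be separated from shared time?** Take a model with a free effect for each participant and for each occasion, and add an indicator for intervention phase. With a common start the indicator is 0, 0, 0, 1, 1 for everyone, which is exactly the sum of the week 3 and week 6 occasion columns. It adds no information. The rank without it is n + (number of occasions) − 1.

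| Schedule | Rank without phase | Rank with phase |
|---|---|---|
| Protocol, n = 4 | 4 + 5 − 1 = 8 | 8 |
| Protocol, n = 10 | 10 + 5 − 1 = 14 | 14 |
| Illustration: 4 people, starts at weeks 0, 1, 2 and 0, with assessments added at weeks 1 and 2 | 4 + 7 − 1 = 10 | 11 |

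Under the protocol's schedule the phase effect cannot be estimated at either end of the sample-size range, so more participants do not help. Staggered starts would make it estimable.

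**3. What this means for the observed pattern.** Assume independent errors with SD 1 and a shift of 1.5 SD after week 0; neither figure is in the documents. Take each person's mean of two later scores minus the mean of three baselines. Its SD is √(1/2 + 1/3) = 0.913, so the chance that one person improves is Φ(1.5/0.913) = Φ(1.643) = 0.950. The chance that all improve is 0.950⁴ ≈ 0.81 for n = 4 and 0.950¹⁰ ≈ 0.60 for n = 10. Simulation (20,000 runs) agrees:

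| Cause of the shift | Mean change | All improve, n = 4 | All improve, n = 10 |
|---|---|---|---|
| Shared time effect, no intervention effect | 1.50 | 82% | 60% |
| Intervention effect, no time effect | 1.50 | 81% | 59% |

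The two rows agree by construction, because with a common start both causes enter the data in the same place. The table illustrates step 2 and is not separate evidence.

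**The case against.** The strongest reply is that the article is open about what it does. It defines its use of the term, gives a purpose for the three pretests and states the simultaneous start. The primary aims are feasibility and acceptability, judged by recruitment, retention, attendance and interviews, none of which needs staggered starts. The outcome analysis is descriptive and visual, and efficacy inference is disclaimed. All of this stands and limits the weight of the point. It does not make the label right. The disclaimer blames the missing comparator and the small sample, and a reader could conclude that more participants under the same schedule would help.

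The three baselines also have real value. They can reveal drift that was already present before the start, and if one assumes such a trend would simply continue, later departures from it can be described. They cannot deal with a shared influence that begins after week 0.

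Some stronger readings are tempting but not supported:

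- A reader might infer that the cited rule demands three staggered replications and that the study has none. The article speaks only of three participants, and the source is not available here.
- A reader might list recovery after cancer treatment as a shared influence. Eligibility covers both active treatment and remission, so recovery would differ between people.
- A reader might see a flat contradiction between the efficacy disclaimer and the Conclusions. The former rules out inferential conclusions; the latter speaks of exploratory, foundational data and defers to a future powered trial. The word *efficacy* is loose but not incompatible.
- A reader might also want the remark on commissioning in Expected Findings removed. It is conditional and forward-looking, and changing it would be a matter of preference.

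**Conclusion.** The point holds as a moderate correction. The design has one phase-change point at any sample size from 4 to 10, and intervention phase is fully confounded with shared time. It is a replicated A-B single-case series with repeated pretests, and the three-participant reason for the sample size does not carry over to it. The group-size reason covers 4 to 10 by itself, so the target need not change.

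This rests on the general definition of a multiple-baseline design (staggered introduction of the intervention) and on allowing shared time effects to take any form. It does not depend on the assumed 1.5 SD. The consequences are confined to the design claim, the sample-size rationale and the interpretation of the secondary outcomes. A reader might infer that the study as a whole is compromised; the documents do not support that, because the feasibility and acceptability results do not use the property that is missing.

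**What to change.** 1. In the Abstract, Study Design, and Strengths and Limitations, describe the design as a replicated A-B (uncontrolled before-after) single-case series with three pretests and a common start.
2. In the sample-size paragraph, remove the three-participant reason and rest the 4 to 10 range on group size and feasibility.
3. Add the common start to the limits already given in that paragraph. State there, and in Strengths and Limitations, that shared time effects (for example season, repeated testing or events in the group) cannot be separated from the intervention.
4. In the Conclusions, replace the reference to preliminary efficacy with individual-level change.

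If the multiple-baseline label is to be kept, start weeks must actually differ between participants or subgroups; varying only the baseline length before a common start would not be enough. Relabelling needs no new data or participants. Its cost is a less favourable description of the design, to be carried through to the final report.

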### Data Collection

All questionnaire data will be collected via Qualtrics. Following submission of the consent form, participants will automatically receive a copy via the platform; copies may also be requested directly from the lead author via email. Participants will be assigned unique identification numbers at enrollment; data will be stored on password-protected university servers and handled in accordance with institutional data governance procedures.

Prior to the start of the online SR intervention, participants who require support with the Microsoft Teams platform will be offered an optional 15-minute tutorial covering how to join a meeting, use the chat and hand-raising functions, and manage audio and video settings. The tutorial will be delivered at a time convenient to each participant.

### Outcome Measures

#### Feasibility and Acceptability

Feasibility will be assessed through recruitment ease and retention rates—including the number of eligible individuals expressing interest relative to the final sample, the time needed to finalize recruitment, the reasons for declining participation or dropping out, and session attendance rates. Acceptability will be explored through postintervention semistructured interviews lasting up to 30 minutes conducted online via Microsoft Teams by a researcher independent to the study team. Verbal informed consent will be obtained and audio recorded prior to the interviews, with timings arranged to accommodate individual preferences, appointment commitments, energy levels, and interviewer commitments. The interview guide can be found in Multimedia Appendix 4.

Intervention fidelity will be assessed using the National Institutes of Health Behavior Change Consortium framework [59], or an equivalent fidelity model, to evaluate adherence, exposure, quality of delivery, participant responsiveness, and the extent to which the intervention was delivered as intended.

#### Individual-Level Preliminary Outcomes

Preliminary individual-level outcomes will be assessed using the Short Warwick-Edinburgh Mental Wellbeing Scale [55], the Kessler Psychological Distress Scale [56], the social domain subscale of the World Health Organization QoL instrument [57], and 2 global QoL items from the European Organisation for Research and Treatment of Cancer Quality of Life Questionnaire Core 30 [58].

### Withdrawal and Dropout

Participation is entirely voluntary, and participants are free to withdraw their consent at any point without needing to provide a reason; doing so will not impact their care or legal rights. If a participant who initially gave informed consent loses the ability to consent during the study (ie, due to progression of their illness), they will be withdrawn from the research. However, any data collected before the loss of capacity will be retained and included in the study unless the participant specifically requests complete data removal.

Withdrawal may take 2 forms: participants may inform the lead author ([name]) of their withdrawal, with the option to either (1) cease all participation, including the intervention, questionnaires, exit survey, and interview; or (2) withdraw from the intervention only while continuing to complete questionnaires and/or the exit survey and/or the interview. Alternatively, participants may withdraw without notification; in this case, the lead author will attempt follow-up contact up to 2 times via email. An exit survey will be administered where possible to all participants who withdraw at whatever point withdrawal occurs to capture dropout reasons.

### Data Analysis Plan

#### Feasibility Measures

Recruitment, attrition, and questionnaire completion rates will be reported descriptively, including 95% CIs where applicable, alongside any observed floor and ceiling effects. Descriptive statistics will include means or medians, SDs or IQRs, frequencies, and proportions as appropriate for the distribution of data.

#### Preliminary Quantitative Outcomes

As this is a feasibility study not powered for inferential testing, preliminary outcomes will be examined descriptively and visually. The reliable change index will be calculated for each outcome measure (Short Warwick-Edinburgh Mental Wellbeing Scale, Kessler Psychological Distress Scale, World Health Organization QoL instrument social domain subscale, and the 2 European Organisation for Research and Treatment of Cancer Quality of Life Questionnaire Core 30 global items). A value of 1.96 or higher will indicate statistically reliable change at the 95% CI, and data will be presented as modified Brinley plots across the 5 time points. This will enable a visual representation of the data across 3 baselines and the midintervention and postintervention time points, consistent with established graphical analysis methods for SCED [60]. Missing data will be handled using a complete-case approach, with the extent and pattern of missing data reported descriptively, as recommended for feasibility studies of this scale [61,62]. As a sensitivity check, outcomes will be examined for participants meeting the minimum attendance threshold (≥3 sessions) compared with the full attendance sample.

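### A complete-case rule can discard usable scores from outcomes analysed one participant at a time, and it sits badly with the commitment to keep data from participants who lose capacity

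*Protocol article*

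**What the plan says.** The Preliminary Quantitative Outcomes section of the protocol article sets the missing-data rule: "Missing data will be handled using a complete-case approach, with the extent and pattern of missing data reported descriptively". The outputs it governs are individual. An RCI is calculated for each measure, with this criterion: "A value of 1.96 or higher will indicate statistically reliable change at the 95% CI". For display, "data will be presented as modified Brinley plots across the 5 time points". The five points are weeks −2, −1, 0, 3 and 6 (Table 2). The only sensitivity check in that section concerns session attendance.

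The Withdrawal and Dropout section says that participants who lose capacity are withdrawn, but that "any data collected before the loss of capacity will be retained and included in the study", unless the participant asks for removal. It also allows participants to "withdraw from the intervention only while continuing to complete questionnaires and/or the exit survey and/or the interview".

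On size, the Participants section says "a formal sample size calculation was not required" and that "this feasibility study will aim to recruit between 4 and 10 participants". One of its two reasons is that "single-case experimental design (SCED) methodology requires a minimum of 3 participants to demonstrate an experimental effect".

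**The concern.** Complete-case analysis is usually chosen because a model needs the same set of observations from everyone. Nothing here has that need. One participant's RCI does not depend on another's scores, and a week-3 RCI does not depend on week 6. Someone with three baselines and week 3 but no week 6 has four scores to plot and a mid-intervention change to report. A complete-case rule can remove some or all of this.

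The second difficulty is consistency. A participant withdrawn for loss of capacity before week 6 cannot be a complete case on either natural reading. The data that the withdrawal section keeps would then be absent from the outcome display.

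At stake is whom the outcome picture describes. The article's realist framework asks for whom the intervention works and expects it to suit some people less than others. Eligibility includes people in active treatment, and the voucher rule anticipates absence through illness or hospital appointments. If missing questionnaires go with illness or poor fit, a completer-only display leaves out the cases that this framework needs. The Discussion would use any sign of benefit to justify larger trials and inform commissioning.

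**Working it through.** **Inputs from the article.** Target N = 4 to 10; a cited design minimum of 3; five assessments per participant. By January 2026, 6 people had registered interest and 2 were eligible, with recruitment running to March 2026. The target comes from no formula, so there is no figure to reproduce.

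**Assumptions.** No completion or dropout rate is given. Let p be the chance that any one assessment is completed, taken as independent, at 80, 90 and 95%. Let d be dropout before week 6. Let q be the chance that a participant counts as complete.

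**Formulas.** The number of complete cases X is binomial(N, q). For N = 4, P(X < 3) = 1 − [4q³(1 − q) + q⁴]. For X to fall below 3, N − 2 participants must be incomplete: 2 of 4, 4 of 6, 6 of 8, 8 of 10.

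**Worked case.** With all five assessments needed and p = 0.90, q = 0.90⁵ = 0.590. Then 4 × 0.590³ × 0.410 + 0.590⁴ ≈ 0.337 + 0.122 = 0.459, so P(X < 3) = 0.541. The expected number of complete cases is 4 × 0.590 = 2.4 at N = 4 and 5.9 at N = 10.

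**Results**, each cell for p = 80/90/95%:

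| Needed to count | q | P(<3), N=4 | P(<3), N=6 | P(<3), N=10 |
|---|---|---|---|---|
| All five (p⁵) | 33/59/77% | 89/54/22% | 69/19/2.6% | 31/1.4/<0.1% |
| One given baseline and week 6 (p²) | 64/81/90% | 45/17/5.0% | 13/1.4/0.1% | 0.6/0.01/<0.01% |
| Any baseline and week 6, (1−(1−p)³)p | 79/90/95% | 19/5.3/1.4% | 1.9/0.1/0.01% | 0.01/<0.01/<0.01% |
| Any baseline and either follow-up, (1−(1−p)³)(1−(1−p)²) | 95/99/99.7% | 1.3/0.07/<0.01% | 0.01/<0.01/<0.01% | all <0.01% |

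The first two rows are readings of the stated rule. The last two show what is usable if every available pair of scores is kept.

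**Dropout only** (q = 1 − d, nothing else missing): at d = 10/20/30%, P(X < 3) is 5.2/18/35% for N = 4, 0.1/1.7/7.0% for N = 6, and at most 0.2% for N = 10. Missed questionnaires that cluster in the same people give results nearer to these than to the p⁵ row.

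**Side check on the fix.** If k baselines with equal, independent errors are averaged, the standard error of the difference from one follow-up is SEM × √(1 + 1/k): 1.41 SEM for k = 1, 1.22 for k = 2 and 1.15 for k = 3. A single standard error for everyone would therefore apply the 1.96 threshold unevenly.

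**The case against.** The strongest reply is that the article never says a complete case needs all five assessments. An RCI compares two scores, so the sentence could mean only that nothing is imputed and that each RCI is computed where both its scores exist. On that reading the plan is already close to the fix, and the registered analysis plan, not shown here, may say so. This stands as a limit on the numbers: the 89/54/22% figures belong to one reading. It does not remove the point, because the sentence as written does not say this, and the two other natural readings both discard usable scores.

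Four stronger inferences are tempting and are not supported.

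- *That everyone who stops is removed.* People may leave the intervention and keep completing questionnaires, so they can still be complete cases. The explicit commitment to keep data concerns loss of capacity.
- *That the two sections flatly contradict each other.* Retained data can still enter the attrition, questionnaire-completion and missingness summaries. The tension is over the outcome display.
- *That the study may fall below its minimum anywhere in the 4 to 10 range.* At N = 10 eight participants would have to be incomplete. The 3 is also cited as a reason for the recruitment target and is not an analysis-set floor; two individual RCIs are not invalid.
- *That results will be biased towards benefit.* The article has no data on who misses questionnaires. The direction is plausible and no more.

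It is also fair that the extent and pattern of missing data will be reported and that inference about efficacy is disclaimed. Reporting the pattern shows who is absent but does not restore their scores.

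**Conclusion.** The concern holds in a limited form. The stated rule does not suit outcomes shown one participant at a time, discards usable scores on either natural reading, and needs reconciling with the section on loss of capacity. The attendance comparison does not repair this, since it sorts people by sessions attended and not by missing questionnaires.

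The size depends on an undefined term and an assumed completion rate. At N = 4 and 90% completion, the chance of fewer than 3 complete cases is 54% if all five assessments are needed and 17% if one baseline and week 6 are needed; 20% dropout alone gives 18%. With two eligible people by January 2026, a sample near the low end is plausible. The p-based figures assume independent completion.

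This should be fixed before analysis. It is not critical: the outcomes are secondary and descriptive, and the primary feasibility and acceptability results do not rest on this rule.

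**What to change.** Replace the complete-case sentence with wording such as:

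> All observed scores of every participant who started are plotted, including those withdrawn after loss of capacity unless they requested removal. RCIs at week 3 and at week 6 are each computed for anyone with that follow-up and at least one baseline. If available baselines are averaged, the standard error of the difference reflects the number of baselines used, and participants with fewer than three baselines are flagged. Improved, unchanged, deteriorated and not observed are counted over all who started. Complete-case results are a secondary display.

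The flag matters because three baselines were planned to establish stability, and a participant with only one gives no evidence of it.

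The change affects analysis wording only, with no added data collection, and the article reports that the analysis has not yet been implemented. The cost is in reporting: the number observed and the precision of each RCI will vary by participant and time point, and both must be shown.
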